## **2.8 Risks and discomforts**

Similar products have been used in Zambia and Democratic Republic of Congo in children of same age with the same health condition. There was no particular serious side effect observed. Thus, in the present study there will be minimal risk to the children. The following are the potential risks and the steps that will be taken to minimize these risks:

- The risk of raw and processed food material contamination with bacteria that can cause diarrhoeal illness. Samples will be analysed to ensure that there is no contamination before the food is dispatched at study sites.
- Food allergies and food sensitivities: allergic reaction to the consumption of peanut has been reported in some countries but not in Malawi. If the children have history of food allergy, they will not be asked to participate.
- Suppression of appetite has been reported for some types of legume and cereal based RUTFs. As per our experience in Zambia and DRC, no such effect occurred with the use of SMS-RUTF and therefore we are not expecting to see this effect in Malawi. However, if this does happen to the children, they will be immediately withdrawn from the study and referred to the health facility for the standard treatment.
- Some children can have loose stools at the beginning of the nutrition therapy with RUTF, especially RUTF containing milk. Usually, the situation resolve spontaneously after one or two days and it does not result to any dehydration and does not delay recovery. In case the children do present such symptoms, they will be monitored carefully and given the appropriate additional treatment if required.
- Study foods have a higher level of iron than the standard food. There is a small risk of some abdominal discomfort at the start of the intake due to the level of iron in the food. However, such complaint was not registered in Democratic Republic of Congo where the RUTFs had the same level of iron. Thus, the risk of this effect occurring is low. If the effect does occur the children will be monitored carefully and given the appropriate additional or alternative treatment if required.
- Blood (3 to 5 ml) will be collected by trained nurses wearing sterile and disposable gloves. Each child sample will be taken with a sterile butterfly needle of appropriate gauge for child age and in vacutainer tubes. Gloves and needles will immediately be disposed of appropriately. Taking the sample will produce a small amount of pain equivalent to a pin prick or a prick similar to the one felt when a sample for malaria test is being collected. The pain experienced will be minimised by thorough training of the tester. All blood samples would be handled in a manner that meets good clinical practices standards[97].

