### **1.5.2.2 Efficacy trial**

Children staying within 1 hour walking distance from feeding points especially established in the community for the study will be enrolled and will be followed up from admission to nutrition recovery using a day care approach. Enrolled children will attend the site daily from 9 am to 3 pm. Children will be offered 200kcal/kg/day of one of the study RUTF. Children will be declared non-recovered if they don't meet the discharge criteria ( $MUAC \geq 12.5$  cm and no oedema) after 3 consecutive months of treatment. Apart from the difference in study therapeutic food, children of all the three study groups will be treated in the same way in accordance with the national guidelines for the treatment of SAM but using the day-care approach as stated above. The day-care approach allows the elimination of several confounding factors such as sharing or poor intake of the therapeutic food at households' level, inappropriate intake of routine medicines and differences in the product acceptance by caregivers that may affect child feeding of the study food. This approach will also allow close monitoring of side effects such as abdominal pain due to iron intake, flatulence (due to unabsorbed sugar), diarrhoea due to lactose intolerance and appetite suppression due to some oligosaccharides. Anthropometric parameters will be measured daily (weight and MUAC) or weekly (height). Clinical conditions will be assessed daily (appetite, oedema, cough, difficulty of breathing, diarrhoea, dehydration, fever, skin eruption, neurological status, anaemia). Embedded sub-studies will allow the assessment of

- haemoglobin (admission and discharge) with an Haemocue device that uses capillary blood collected at finger prick;
- body composition using deuterium dilution technique (at discharge for both those who recovered and those who did not recover);
- body composition using bio-electrical impedance analysis (at admission or when oedema subside, at time of reaching discharge criteria, at discharge and at 3 months follow up) using a Bodystat 1500 MDD device;
- breast milk intake using the dose-to-mother deuterium oxide dilution technique in children still breastfed at admission (two weeks after the start of the treatment);
- stool calprotectin using a quantitative point-of-care chromatographic immunoassay kit for the assessment of intestinal inflammation (admission, 28 days after the start of treatment, at discharge)

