Previous to the first randomised study conducted in Zambia, a formal acceptability and tolerance trial was conducted comparing SMS-RUTF and P-RUTF among 45 children aged 4-11 years. The SMS-RUTF was as acceptable as the P-RUTF with no associated adverse effects[90]. For the second randomised trial conducted in Democratic Republic of Congo (DRC), we assumed that the changes made to the formulation would not affect acceptability and tolerability. Thus, no formal acceptability trial was conducted. The results obtained regarding

frequency of diarrhoea, flatulence, vomiting, skin eruption and RUTF intake confirmed that SMS-RUTF was as accepted as P-RUTF (paper in preparation). The only difference observed was in intake and this difference was not of clinical relevance [214g/day (167kcal/kg/day) for P-RUTF versus 199g/day (152kcal/kg/day) for SMS-RUTF in children below 24 months and 276g/day (157kcal/kg/day) for P-RUTF versus 251g/day (139kcal/kg/day) for SMS-RUTF for children 24 months and more). For the present study, it is anticipated that the addition of the AA mixture will modify significantly the taste of the product. It is also well-known that the addition of milk powder makes the product sweeter.

Data on the efficacy of milk free RUTF in treating SAM in children are scarce. Valid has successfully conducted two randomised studies on the subject. These results showed that FSMS-RUTF was effective in children two years and above but not among children less than two years. [91]. Based on the results of that study, the formulation of FSMS-RUTF has been optimised

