#### Other secondary hypotheses:

- 6 Haemoglobin gain of children treated for SAM with FSMS-RUTF will not be lower than that of children treated with MSMS-RUTF nor than that of those treated with P-RUTF given a margin of non-inferiority of 0.5g/dl.
- 7 The RUTF daily intake in grams and in kcal/kg/day of children 6 to 59 months old treated for SAM with FSMS-RUTF will not be inferior to the daily intake of children of the same age treated with MSMS-RUTF nor to the daily intake of those treated with P-RUTF given a margin of non-inferiority of 18g/day and 25kcal/kg/day, respectively (age group 6 to 23 months and 24 to 59 months to be sampled and analysed separately).
- 8 Breast milk intake of children 6 to 23 months old treated for SAM with FSMS-RUTF will not be lower than the breast milk intake of children of the same age treated with MSMS-RUTF nor to the intake of those treated with P-RUTF given a margin of non-inferiority of 100g/day.
- 9 Proportion of children with normalised stool calprotectin at 14 days, 28 days and recovery will not be lower in children treated for SAM with FSMS-RUTF than in those treated with MSMS-RUTF or in those treated with P-RUTF given a margin of non-inferiority determined using the synthesis method based on the confidence interval observed in children treated with P-RUTF.
- 10 Plasmatic level of key growth related AA of children treated with FSMS-RUTF will not be inferior to that of children treated with MSMS-RUTF or P-RUTF given a margin of non-inferiority defined using the synthesis method
- 11 12-months after discharge survival in children with SAM treated with FSMS-RUTF will not be inferior to that of children treated with MSMS-RUTF nor to that of those treated with P-RUTF given a margin of non-inferiority of 10%.

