#### 2.5.1.2 Efficacy trial

As stated in the hypotheses the main study will be a 3 group statistician blinded, randomized and controlled, parallel groups, **efficacy** non-inferiority trial. Because the participants will be able to distinguish the different RUTFs based on colour and mouth feel, participants will not be blinded. We will use the day care approach to ensure that children eat only the RUTF of the group to which they have been assigned. No study food will be taken home and the intake will be supervised by study enumerators who will in person feed the children.

The principal endpoints for the efficacy trial are:

1. Recovery rate
2. Mean weight gain
3. Mean time to recovery
4. Mean height gain
5. Percentage of body fat mass at recovery

6. Mean phase angle
7. Prevalence of anaemia
8. Incidence of deaths after discharge

The definition of principal endpoints is given below

(a) Recovery rate

The recovery rate will be measured as a percentage of those children who are discharged cured from the OTP programme divided by the total number of children who exit from the programme

$$\text{Recovery rate} = \frac{\text{No. children discharged Cured}}{\text{Total No. of Exit}} \times 100$$

(b) Average weight gain

The average weight gain will be measured as the mean of the growth velocity expressed in g/kg/day of individual children calculated as follow:

$$\text{Weight gain} = \frac{\text{Discharge weight (g)} - \text{Admission weight (g)}}{\text{Admission weight (kg)} \times \text{Length of stay (days)}}$$

$$\text{Average weight gain} = \frac{\Sigma \text{ weight gains}}{\text{Total children}}$$

(c) Average time to recovery or Length of stay

The average length of stay (LOS) is the mean of the LOS expressed in days of individual children calculated as follow:

$$\text{Average LOS} = \frac{\Sigma (\text{Discharge date} - \text{Admission date})}{\text{Total of children}}$$

(d) Average height gain

The average height gain is the mean of the height gain expressed in centimetres of individual children calculated as follow:

$$\text{Average height gain} = \frac{\Sigma (\text{Height 3 months after discharge (cm)} - \text{Admission height (cm)})}{\text{Total of children}}$$

(e) Prevalence of anaemia

The prevalence of anaemia will be expressed in percentage and calculated as follow

$$\% \text{ anaemia} = \frac{\text{n haemoglobin} < \frac{11.0\text{g}}{\text{dl}} * 100}{\text{total children with results}}$$

(f) Incidence of death after discharge

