## **2.6 Ethical considerations**

The study will be conducted in compliance with the Declaration of Helsinki. Permission for the trial to be conducted will be obtained from the Malawi National Health Sciences Research Committee and the Ajinomoto institutional review board. Participation will be voluntary. At the time of admission, each child's parent or carer will be informed about the nature and purpose of the study and asked for their verbal and written consent for their child to be included in the study and for their medical information to be used for research purposes. The caregivers will be informed that participation is voluntary and this information will be emphasised again on the information sheet. The carer information sheet and the consent form will be in English but will also be translated in Chichewa, the national language. The sheet will contain information on the study objectives, study procedures, anticipated duration of participation, potential risks and discomfort for the child, benefits for the child and for the under five population in general, conditions of study termination or participant withdrawal, confidentiality of records and contact persons if any question or problem arise. When parents or carer withhold consent for participation, children will be referred to non participating clinics providing care for SAM children. There are several such clinics in the selected Districts. They use standard P-RUTF. Any child who will develop study food related side effects or any serious disease during the study will be referred to the appropriate level of care and the cost of the treatment met by the research project.

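### Protocol 2.8 ends study participation, not only the study food, for a child with appetite suppression, so later measurements on that child would be lost

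*Protocol*

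**What the plan says.** Section 2.8 lists the foreseen risks and the response to each. For appetite suppression, which it says has been seen with some legume and cereal RUTFs, the response is that "they will be immediately withdrawn from the study and referred to the health facility for the standard treatment". It adds that none occurred with the earlier SMS-RUTF in Zambia or DRC and that none is expected in Malawi.

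Other side effects are handled differently. Loose stools, linked especially to milk-containing RUTF, are monitored and treated. For abdominal discomfort from iron: "If the effect does occur the children will be monitored carefully and given the appropriate additional or alternative treatment if required". Section 2.6 adds a general rule that a child developing "study food related side effects or any serious disease during the study will be referred to the appropriate level of care", at the project's cost. Neither mentions leaving the study.

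Appetite is assessed daily. Section 1.5.2.2 says the day-care approach allows close monitoring of effects that include "diarrhoea due to lactose intolerance and appetite suppression due to some oligosaccharides". RUTF intake is tested under hypothesis 7 in section 2.3.2.2, "given a margin of non-inferiority of 18g/day and 25kcal/kg/day". The foods can be told apart: "Because the participants will be able to distinguish the different RUTFs based on colour and mouth feel, participants will not be blinded".

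On the previous food, section 2.2 reports: "The only difference observed was in intake and this difference was not of clinical relevance". For the new food, "it is anticipated that the addition of the AA mixture will modify significantly the taste of the product".

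**The concern.** Stopping a food that a child will not eat is right. Stopping observation of that child is a separate decision, and section 2.8 joins the two. The children affected would be those who tolerate the food worst, so the missing data would be related to outcome. They could also be uneven between arms, because the trigger is tied to the type of food under test and is judged by staff who feed the child and can see which food it is.

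At stake are measurements due after the withdrawal: height at 3 months, later MUAC and oedema status, discharge measurements (haemoglobin, body composition, bio-impedance, calprotectin) unless they happen to be taken at withdrawal, and vital status if follow-up covers every child discharged alive. An analysis plan can decide how to handle missing values, but it cannot recover measurements that the conduct rule prevented.

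**Working it through.** The plan gives no figure for these withdrawals, so there is none to reproduce. The check is mainly a comparison of text.

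**1. How each listed risk is handled (section 2.8)**

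| Risk | Response | Participation ends? |
|---|---|---|
| Food contamination | Test the food before dispatch | No |
| Food allergy | Not enrolled if there is a history | Not applicable |
| Appetite suppression | Withdrawn from the study, referred | Yes |
| Loose stools | Monitor, treat | No |
| Iron-related discomfort | Monitor, additional or alternative treatment | Not stated |

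The general rule in section 2.6 is referral without withdrawal. Blood sampling, the last item in the list, is a procedure and raises no such question.

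**2. Is follow-up after withdrawal provided elsewhere?** Section 2.12 plans visits 3 and 12 months after treatment ends, for children eligible for follow-up. It does not say that a withdrawn child is eligible. I found no other provision. Sections 2.9 and 2.13 were not in the text available to me.

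**3. Can zero or equal numbers by arm be assumed?** Earlier intake, section 2.2, P-RUTF against SMS-RUTF:

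- Under 24 months: 214 − 199 = 15 g/day (15/214 = 7%); 167 − 152 = 15 kcal/kg/day.
- 24 months and over: 276 − 251 = 25 g/day (25/276 = 9%); 157 − 139 = 18 kcal/kg/day.

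The margins in hypothesis 7 are 18 g/day and 25 kcal/kg/day. Lower mean intake is not appetite suppression, and the protocol judged the gap clinically unimportant. Together with the expected change in taste, it means only that zero or equal counts are not assured.

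**4. Illustration for 3-month height.** Let w be the share of one arm withdrawn (assumed) and d the shortfall of those children against the rest (assumed to be 1 SD). With m the mean of the children still observed, the mean of all is (1 − w)m + w(m − d) = m − wd. The observed mean is therefore too high by wd. SDs are from Table 2 (0.7 and 0.8 cm). The margin is 0.5 cm in section 2.3.2.2; Table 2 uses 0.3 cm for the older group.

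| w | Children of 250 / 150 | 6-23 months: 0.7w cm (share of 0.5) | 24-59 months: 0.8w cm (share of 0.5; of 0.3) |
|---|---|---|---|
| 0 | 0 / 0 | 0 | 0 |
| 1% | 2.5 / 1.5 | 0.007 (1%) | 0.008 (2%; 3%) |
| 2% | 5 / 3 | 0.014 (3%) | 0.016 (3%; 5%) |
| 5% | 12.5 / 7.5 | 0.035 (7%) | 0.040 (8%; 13%) |

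The 10% loss already allowed for is 25 and 15 children per arm, so 5% would add half as much again.

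**5. Outcomes that survive the rule.** Recovery rate is cured children over all exits (section 2.5.1.2). A referred child is most naturally an uncured exit, and then no outcome is missing. Weight gain uses admission weight, exit weight and length of stay. Weight is taken daily, so it can be computed to the day of exit.

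**The case against.** The strongest reply is that the group will probably be empty. No case was seen in two earlier trials. Persistence of good appetite is an acceptability criterion in phase 1 (sections 1.5.4.1 and 2.5.1.1), and section 2.3.1 has the recipe refined to address any side effect before the efficacy trial. This largely stands. It is not a guarantee: phase 1 puts 40 children on each test food, and zero cases in 40 leaves a one-sided 95% upper limit of 1 − 0.05^(1/40) = 7.2%, in children aged 3 to 5 years without SAM.

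Second, the different handling has a clinical reason. Loose stools usually settle in a day or two, whereas a child who will not eat cannot be treated with the food. The alternative treatment allowed for iron discomfort may also mean leaving the study food. This justifies stopping the food; it does not justify ending observation.

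Third, data after referral are impure. Section 2.6 says non-participating clinics use P-RUTF, so later growth in a test-arm child would partly reflect the control food and could pull the arms together. This stands, and it is a real cost of the fix. It also means that follow-up might show a smaller shortfall than the 1 SD assumed above.

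A reader might infer more than the documents support:

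- **Biased recovery rate, or a raised risk of falsely declaring non-inferiority.** This would need such children to be left out of the exits or out of a deciding per-protocol set. The protocol says neither.
- **Inflated weight gain.** This would need the child to be dropped from the mean although an exit weight exists.
- **Survival left unknown.** Section 1.5.2.2 times mortality from nutritional recovery and section 2.5.6.2.1 compares children who recovered, so an uncured child may be outside that analysis anyway. Hypothesis 11 and section 1.5.3.2 (children discharged alive) are looser, so vital status is lost on one reading only.
- **Loss of power.** Counting such children as uncured follows from the natural reading of the recovery definition, whatever section 2.8 says about follow-up.

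**Conclusion.** The point holds in a limited form and is minor. Section 2.8 ends participation for one side effect only. That effect is close to a tested outcome and is linked by the protocol to the type of food under test, and nothing available provides for data afterwards. The clearest loss is 3-month height, together with later MUAC and oedema status and discharge measurements.

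The size is nil if no case occurs, which is what the protocol expects. Under an assumed 1 SD shortfall, it is 1-3% of the 0.5 cm height margin when 1-2% of one arm is withdrawn, and 7-8% when 5% is (13% of the 0.3 cm in Table 2 for the older group). The withdrawal rates and the shortfall are assumptions with no source in the protocol. No bias in the primary recovery rate is shown, and no size is put on weight gain, survival or power.

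**What to change.** In section 2.8, replace the withdrawal wording with: *study food stopped and child referred for standard treatment, in all three arms alike; participation continues where the child can be reached, with discharge status, 3-month height and vital status collected at the visits already planned.* In section 2.5.1.2(a), add that such a child counts as an uncured exit at the food stop, stays in the recovery-rate denominator, and remains in the ITT analysis.

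Report measurements after the stop as post-discontinuation data within ITT, alongside the per-protocol analysis, because they partly reflect P-RUTF and may dilute differences between arms.

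The cost is two short edits and some tracing of referred children. Eligibility requires residence within an hour's walk of the centre (section 2.5.2.2), and visits at 3 and 12 months are already planned (section 2.12). Clinical protection is unchanged. RUTF intake after the stop is not recovered.

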## 2.10 Confidentiality and dissemination of findings

Confidentiality of each study participant will be maintained at all times through the allocation of a unique identification number that will be used in the electronic database storing the data. Sufficient attention will be paid to protect the rights and individual information of subjects.

A final report will be produced at the end of the research. Other means of dissemination will include presentation of findings to relevant policy makers, presentation in local and international meetings and publication in peer reviewed scientific journals. The journals that will be targeted include The American Journal of Clinical Nutrition, The Lancet, Maternal and Child Nutrition and PLOS Medicine. During the process of publication sufficient attention will be paid to protect the rights and individual information of subjects.

## 2.11 Data ownership and access

The Government of Malawi own the data and will retain the right to oppose any utilisation of the data that it considers inappropriate, not covered by the ethical approval or that the country authorities regard as misrepresenting the facts. Valid Nutrition and Ajinomoto the sponsor, will have free access to the data, including data of samples analysed abroad. They will have equal right in the management and utilisation of the data.

## 2.12 Schedule

For the acceptability trial, each child will be followed up for 6 consecutive weeks that include a period of washout of two weeks during which no measurement is taken. For the efficacy trial, children will be followed from the start of treatment until cure that takes approximately 2 months but will be 3 months for the non-respondents. Children eligible for follow up after discharge will be visited twice after the treatment ended. This will be 3 months and 12 months after the end of treatment. Consequently, the study will cover the period from February 2015 to March 2016 for the intervention period as indicated in the table 6 below but the follow up after discharge will only be completed in March 2017.

